## 2. Materials and Methods

### 2.1. Study Design and Setting

The overall design of the study is represented in Figure 1. The MED4Youth study is a multicenter single-blinded randomized controlled clinical trial with obese and overweight adolescents (13–17 y) from Italy, Portugal, and Spain, in which an MD-based intervention will be compared to a traditional low-fat diet intervention. The three centers involved in the study obtained the approval of the Ethics Committee of each institution: (1) Eurecat (study coordinator): Institut d’Investigació Sanitària Pere i Virgili (Ref. CEIM: 210/2020); (2) UNIPR: Area Vasta Emilia Nord (AVEN) Ethical Committee (pre-approval Ref. Prot. 28638); (3) UC: Ethics Committee of Centro Hospitalar e Universitário de Coimbra and Portuguese National Data Protection Commission (Ref. CHUC-197-20). MED4Youth study was registered at ClinicalTrials.gov (NCT04719052). The protocol conformed to the Helsinki Declaration and Good Clinical Practice guides of the International Conference of Harmonization. This study followed the CONSORT criteria.

According to the sample size calculations, a total of 240 volunteers from Italy, Portugal, and Spain will be recruited for this study (80 participants per country).

The Spanish subjects will be recruited by Eurecat in the province of Tarragona, the Portuguese subjects will be recruited by the Hospital Pediátrico de Coimbra, and the Italian subjects will be recruited by the Pediatric Clinic of the Maternal and Child Department of the Parma University Hospital. The 80 individuals recruited in each country will be randomly assigned to either a MD group (n = 120, n = 40 per country), which will be instructed to follow an MD that will incorporate sourdough bread, hummus, pomegranate, and mixed nuts, or a Control group (n = 120, n = 40 per country), which will be assigned to a standard low-fat diet. The intervention duration is 4 months for each participant, including 3 visits. A follow-up visit after 4 months from the end of the intervention will be carried out.

The randomization code will be computer-generated using software (Geoffrey C. Urbaniak and Scott Plous, Lancaster, PA, USA). Furthermore, the unit responsible for the randomization will be separate from the study researchers.

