### 2.7. Outcomes

The primary outcome is the BMI z-score, which is a standardized measure of BMI based on specific age and sex [50,51]. The effectiveness of the intervention will be evaluated by comparing the BMI z-score between the control (low-fat diet) and intervention (MD) groups.

The secondary outcomes are:MD adherence, using the KidMed questionnaire [19]Physical activity, using Physical Activity Questionnaire for Adolescents (PAQ-A) [52]Dietary intake and habits:
○3-day dietary records [53]○Food frequency questionnaire (FFQ) of the Helena study [53]
Nutritional knowledge, using the NK Helena questionnaire [54]Quality of life, using the kidscreen-27 Index [55]Sociodemographic data, using the Health Behavior in School Age Children (HBSC) socio-demographic questionnaire [56]Anthropometric data: weight, height, BMI (weight/height^2^), body composition using bioimpedance, waist circumference (WC), and waist–hip ratio (WHR)Blood pressureBiochemical variables, gut microbiota composition, and metabolomics in urine, blood, and feces

All outcomes are presented and summarized in Table 2.

The questionnaires will be used to collect data on the habits and knowledge of the participants in different visits. These data will be collected through the app and then combined with anthropometric and food intake data to assess possible associations among these variables.

At visit (V)1, V2, V3, and V4, the subjects will attend the partner center in over-night fasting conditions to evaluate anthropometric parameters, dietary intake, physical activity, and blood pressure. At V1 and V3, feces, blood, and morning urine will be collected to perform the analyses of microbiota and gut-derived metabolites; food intake biomarkers and phenolic metabolites; circulating levels of glucose and blood lipid profile, biomarkers of insulin resistance, adipose tissue function, inflammation, oxidative stress, and cardiovascular risk, and advanced glycation end products (AGEs). In addition, the lipid profile of the erythrocyte membrane will be assessed at V1 and V3. Data collected at V4 will be used to investigate if the intervention will have changed medium-term dietary habits, having a medium-term impact also on blood pressure and anthropometric parameters. Additionally, for female adolescents, information about their menstrual cycle will be recorded in each visit. Table 3 shows the schedule of each visit, which will follow the same timeline for each enrollment center.

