### 2.8. Sample Size

According to the sample size calculations based on differences in BMI z-score (primary outcome) between groups (0.2 difference with 80% power; two-tailed α: 0.05; standard deviation: 0.5; dropout rate: 20%), a total of 240 volunteers from three Mediterranean countries (Spanish, Portugal and Italy) will be recruited for this study (80 participants per country) after obtaining the approval of the Ethics Committees of each recruiting center and the written informed consent from parents and from subjects.

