### 2.9. Statistical Analyses

#### 2.9.1. Univariate Data Analysis

Data will be expressed as mean ± standard deviation (SD). Grubbs’ test will be used to detect outliers, which will be discarded before subsequent analyses. The normality of variables will be assessed by the Kolmogorov–Smirnov test. Non-parametric variables will be log transformed. Differences in baseline characteristics between subject groups will be analyzed by analysis of covariance (ANCOVA), in which dietary intervention group assignment (G) will be used as a fixed factor and the variables age and sex will be included as covariates. Analyses will be made by intention-to-treat. An ANCOVA model will be used to analyze the data at the end point. The anthropometric and biochemical parameters (changes from baseline) will be used as dependent variables, dietary intervention (MD; low-fat diet) will be included as fixed factor, and the variables age and sex, as well as baseline values, will be included as covariates. Within each group (MD and low-fat diet), changes from baseline will also be analyzed at the end point by a paired *t* test. Within each group (MD and low-fat diet), changes from baseline will also be analyzed considering the different time points using a general linear model for repeated measures. All statistical analyses will be performed with SPSS Statistics (SPSS, Inc., Chicago, IL, USA), setting the level of statistical significance at bilateral 5%. For metagenomics analysis, the non-parametric Mann–Whitney U test will be performed to elucidate pairwise differences on bacteria relative abundance among dietary groups. The Benjamini–Hochberg method will be used to adjust P values for multiple testing considering a 5% false discovery rate. Statistical analyses will be conducted with open-access STAMP software.

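### The follow-up question at V4 has no between-diet comparison: the only stated model that uses V2 and V4 is fitted separately within each arm

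*Protocol article*

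**What the plan says.** Section 2.7 gives the follow-up visit a causal question: "Data collected at V4 will be used to investigate if the intervention will have changed medium-term dietary habits". The same sentence extends it to blood pressure and anthropometric measures. Table 2 schedules these measures, and the dietary and adherence questionnaires, at all four visits.

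Section 2.9.1 then sets out three univariate analyses of change:

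- A between-diet model: "An ANCOVA model will be used to analyze the data at the end point". Diet is the fixed factor, with age, sex and baseline as covariates. Its outcomes are defined by: "The anthropometric and biochemical parameters (changes from baseline) will be used as dependent variables".
- A paired t test within each arm, also at the end point.
- A repeated-measures general linear model, again by arm: "Within each group (MD and low-fat diet), changes from baseline will also be analyzed considering the different time points".

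The article does not tie the end point to a numbered visit. Table 3 describes V3, at four months, as the last visit of the study proper, and V4 as a visit four months after the intervention ends. V3 is therefore the natural reading.

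**The concern.** The stated analysis cannot answer the stated aim. Whether the intervention had a lasting effect is a question about the difference between randomised arms at V4. The only model that could take in V4 data looks at one arm at a time, so the randomisation plays no part in its result.

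Within-arm change is a poor substitute here for four reasons found in the article:

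- There is no untreated control (section 2.1), so no arm shows what would have happened without treatment.
- Entry requires a BMI at or above the 90th percentile (section 2.2), so some regression to the mean is expected in both arms.
- Participants are 13 to 17 years old and growing. The BMI z-score allows for age and sex, but weight, waist and blood pressure do not.
- Both arms receive the motivational interview and the web-application (sections 2.4 and 2.5). A change in reported habits within one arm may come from these and not from the diet.

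The risk is a claim of persistence for the Mediterranean diet based on a significant change in one arm and a non-significant change in the other.

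**Working it through.** **Step 1: which visits enter which between-diet analysis.**

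| Analysis | Diet term? | Visits |
|---|---|---|
| ANCOVA of change | yes | end point (read as V3) |
| Paired t test | no, by arm | end point |
| Repeated-measures GLM | no, by arm | the several time points |
| Mann-Whitney, OPLS-DA, DIABLO (sections 2.9.1 to 2.9.3) | yes | centred on microbiota and metabolite data, collected at V1 and V3 only (Table 2) |

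No row has both a diet term and V2 or V4. In addition, two of the three V4 targets, dietary habits and blood pressure, are not named as dependent variables of the ANCOVA.

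**Step 2: what separate within-arm tests can show.** Suppose both arms have the same true change and the same power p to detect it. The arms are independent, so P(exactly one significant) = 2p(1-p).

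| Assumed p | 2p(1-p) |
|---|---|
| 0.3 | 2 × 0.3 × 0.7 = 0.42 |
| 0.5 | 2 × 0.5 × 0.5 = 0.50 (the maximum) |
| 0.8 | 2 × 0.8 × 0.2 = 0.32 |
| 0.9 | 2 × 0.9 × 0.1 = 0.18 |

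To tie p to this trial, take 96 per arm (120 × 0.8, from the planned size and dropout). The SD of the change is not given, so 0.3 and 0.5 are assumptions; 0.5 is the SD used for the sample size. Two-sided paired t test at 5%:

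| True change in each arm | SD of change | Power p | 2p(1-p) |
|---|---|---|---|
| 0.06 | 0.3 | 0.49 | 0.50 |
| 0.06 | 0.5 | 0.21 | 0.34 |
| 0.10 | 0.3 | 0.90 | 0.18 |
| 0.20 | 0.5 | 0.97 | 0.05 |
| 0.20 | 0.3 | about 1 | about 0 |

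The risk is largest for modest changes and vanishes for large ones. In the last row both arms are significant, which still says nothing about the difference between diets.

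**Step 3: whether a V4 contrast is feasible with the planned numbers.** The sample-size inputs are a difference of 0.2, SD 0.5, 80% power, two-sided 5% and 20% dropout (section 2.8).

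- n per arm = 2 × [0.5 × (1.960 + 0.842) / 0.2]² = 98.1.
- Dividing by 0.8 gives 122.6, so 123 per arm or 246 in all. The t-based 100 per arm multiplied by 1.2 gives 240. The stated 240 is reproduced closely enough and is not in dispute.
- With 96 per arm: 0.2 / (0.5 × √(2/96)) = 2.771; 2.771 - 1.960 = 0.811; power 79.1%.

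Loss by V4 is not stated separately. If it were also 20%, with SD 0.5, a V4 contrast would have that same 79% power for 0.2. At 30% loss (84 per arm) the ratio is 2.592 and power 74%; at 40% loss (72 per arm) it is 2.400 and power 67%.

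**The case against.** The strongest reply is that within-arm analyses are announced as additional. Section 2.7 says effectiveness will be judged by comparing the BMI z-score between groups, and nowhere do the authors say they will set one arm's p value against the other's. The primary question has a randomised, baseline-adjusted comparison, and a V4 ANCOVA could be written in a fuller document that is not shown. The first part stands: it limits the point to secondary follow-up results. The last part does not remove it. The article is not silent on the multi-visit analysis; it states one and makes it within-arm.

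It is also fair that 50% is the ceiling of 2p(1-p) and should not be quoted alone. The range is shown for that reason.

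A reader might go further and infer that the end-point ANCOVA uses completers only, so that the intention-to-treat claim is not delivered. The document does not support this. It states intention-to-treat, mentions no complete-case rule and says nothing on missing values, which are commonly dealt with in an analysis plan. A change-score ANCOVA is compatible with imputation. Up to 48 of 240 participants could lack a V3 value at the planned 20% dropout, but how they would be handled is unknown.

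A reader might also infer biased dropout from the limitation that controls receive no foods. Section 3 draws from it only that adherence to the control diet may be lower. It does not say that controls will leave more often, and section 2.8 gives one dropout rate for both arms.

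**Conclusion.** The point holds in limited form. On the natural reading of the end point as V3, no stated analysis compares the diets at V2 or V4, although section 2.7 asks of V4 whether the intervention had a medium-term effect. Dietary habits and blood pressure also lack a named between-diet analysis.

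If within-arm results were used to fill the gap, two arms with equal true change would disagree on significance in 18% to 50% of trials for within-arm power between 0.9 and 0.5. These powers are assumptions. The figure is lower when changes are large relative to their SD.

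The consequence is confined to the secondary conclusions about persistence. The V3 between-diet comparison of the primary outcome is not impaired by this point, and no claim is made about completers, intention-to-treat or dropout bias.

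**What to change.** - State that the end point is V3 and keep the V3 between-diet contrast as primary.
- Add a between-diet comparison at V4, and at V2. Either of two forms will do: the same ANCOVA of change at each visit, adjusted for baseline, age and sex; or one repeated-measures mixed model over V2, V3 and V4 with diet, visit, diet-by-visit, baseline, age and sex, reporting the diet contrast at each visit.
- Name dietary habits and blood pressure as dependent variables of that analysis.
- Report within-arm changes as estimates with confidence intervals, for description only, and drop the within-arm tests as evidence about a diet.

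The cost is a few sentences and a little extra analysis. No new visit, measurement or participant is needed, since the data are already scheduled. The mixed model is optional: it also uses partial data from participants who miss a visit, at the price of a missing-at-random assumption. Repeating the ANCOVA at V4 is enough to close the gap.

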All the above commented aspects prompted us to build a multidisciplinary consortium of six partners from five Mediterranean countries, with complementary expertise and resources within the areas of nutrition, biochemistry, ICT/Bioinformatics, omics sciences, and food manufacturing, which was created to implement a strategy to tackle youth obesity (MED4Youth project; https://med4youth.eu/ (accessed on 12 April 2021)). This consortium is constituted by four research institutions: Fundació Eurecat (Reus, Spain), University of Coimbra (UC, Coimbra, Portugal), Università di Parma (UNIPR, Parma, Italy) and Scientific Food Center (Amman, Jordan), and two small and medium enterprises (SMEs), NOVAPAN S.L. (Spain) and Shikma Field Crops (Israel). The MED4Youth project arises with the main purpose of assessing whether an energy-restricted MD intervention including healthy and palatable products from the Mediterranean basin (mixed nuts [10], pomegranate [35,36,37], and hummus [38]) and a multigrain sourdough bread with proven health effects [39] is more effective against youth obesity and associated CVD risk factors than a conventional low-fat diet. To achieve this goal, a multicentric nutritional and clinical intervention study, specifically targeting obese/overweight adolescents (13–17 years) from Spain, Italy, and Portugal will be carried out. The study will include an educational approach based on a web-application designed to encourage healthy behaviors. Furthermore, the project will also include an omics and a system biology approach to elucidate whether the MD can shape the gut microbiota and gut-derived metabolites, to shed more light on the mechanisms by which MD may exert its beneficial effects against youth obesity and CVD risk factors.

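### The between-diet test of bacterial taxa makes no stated use of the baseline stool sample or of country, which probably costs power on a secondary, mechanistic outcome

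*Protocol article*

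**What the plan says.** For the metagenomic data, Section 2.9.1 of the protocol article states that a Mann–Whitney U test "will be performed to elucidate pairwise differences on bacteria relative abundance among dietary groups". It continues: "The Benjamini–Hochberg method will be used to adjust P values for multiple testing considering a 5% false discovery rate". The software named is STAMP. The p values are therefore adjusted for multiplicity, but no covariate, stratum, change score or visit is named.

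Earlier in the same paragraph the other outcomes are treated differently. For the endpoint ANCOVA, "The anthropometric and biochemical parameters (changes from baseline) will be used as dependent variables", and "the variables age and sex, as well as baseline values, will be included as covariates".

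The baseline data for taxa will exist. Section 2.7 says: "At V1 and V3, feces, blood, and morning urine will be collected to perform the analyses of microbiota and gut-derived metabolites". Table 2 schedules 16S sequencing at both visits. Section 2.1 allocates the 80 participants of each country 40 to each diet.

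Section 2.7 lists gut microbiota composition among the secondary outcomes. The Introduction makes it a mechanistic aim to "elucidate whether the MD can shape the gut microbiota and gut-derived metabolites".

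**The concern.** Whether a diet shapes the microbiota is a question about what happens between V1 and V3. People can differ in a taxon before the diet starts, and so can countries. A two-sample Mann–Whitney test takes no covariates. If it is applied to V3 abundance, all of that prior variation stays in the noise. The article does adjust for baseline, age and sex for the anthropometric and biochemical outcomes.

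Sections 2.9.2 and 2.9.3 do not fill the gap. Hierarchical clustering, PCA, PLS-DA and DIABLO describe clusters or discriminate between groups. None states a baseline- or country-adjusted comparison of a taxon between diets.

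At stake is the chance of detecting real diet effects on individual taxa, in a setting where false discovery rate control already makes the per-taxon threshold strict.

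**Working it through.** **1. The plan's own figure.** The article gives no power or sample size for the microbiota. The only calculation (Section 2.8) is for BMI z-score: difference 0.2, SD 0.5, 80% power, two-sided 5%, 20% dropout.

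- n per arm = 2 × (1.96 + 0.84)² × (0.5/0.2)² ≈ 98.1, so 99 per arm and 198 in total.
- Adding 20%: 99 × 1.2 ≈ 119 per arm, 238 in total.
- Dividing by 0.8: 98.1/0.8 ≈ 123 per arm, 246 in total.

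The stated 240 is reproduced closely, but it says nothing about taxa.

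**2. Assumptions for a taxon.** The documents give neither the V1–V3 correlation r nor the share of variance between countries, so ranges are shown. For power I assume an effect of 0.4 SD (borrowed from 0.2/0.5), 96 evaluable per arm (120 × 0.8) and a two-sided 5% test of one taxon.

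**3. Value of the V1 sample.** Relative to V3 alone, the variance of the diet contrast is 1 − r² with linear baseline adjustment and 2(1 − r) for a change score. The gain in effective sample size from adjustment is 1/(1 − r²) − 1. The last three columns are simulated power with no country effect (1,500 replicates).

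| r | 1 − r² | Gain in effective n | 2(1 − r) | Mann–Whitney, V3 | Rank ANCOVA on V1 | Mann–Whitney, change |
|---|---|---|---|---|---|---|
| 0 | 1.00 | 0% | 2.0 | 77% | 77% | 49% |
| 0.3 | 0.91 | 10% | 1.4 | 77% | 82% | 65% |
| 0.5 | 0.75 | 33% | 1.0 | 76% | 87% | 78% |
| 0.7 | 0.51 | 96% | 0.6 | 77% | 95% | 92% |

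The linear formula agrees on the gain from adjustment: power 79%, 83%, 89% and 97% at the four correlations. So adjustment is worth about 0, 4, 10 and 18 points of power. A change score is no better than V3 alone at r = 0.5 (78% against 76%, within simulation error) and is worse below that.

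**4. Stricter thresholds.** At a per-taxon threshold of 0.005, used only to illustrate what false discovery rate control can imply, the linear formula gives 49% unadjusted against 54% (r = 0.3), 65% (r = 0.5) and 86% (r = 0.7).

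**5. Value of country.** Multiplying the variance by (1 − share explained by country) raises formula power from 79% to 83% at a 10% share and to 87% at 20%. That is 4 to 8 points for country on its own. Part of this is already carried by V1. In simulation, adding country to rank ANCOVA gave about 0 to 5 further points.

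**6. Validity.** With no diet effect (1,000 replicates per setting), the Mann–Whitney test on V3 rejected in 2.5% to 5.4% of runs. It was at or near 5% without a country effect and mostly below it with one. There is no sign of excess false positives.

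**The case against.** **No visit is named.** A reader might infer that the V1 samples are discarded and that the test is a V3-only contrast. The text does not say that. A test on change is not excluded, and Section 2.9.3 speaks of changes brought about by the intervention. V3 abundance is the likelier reading, because the same paragraph names change from baseline where it means it. The documents support only that no use of V1 is stated.

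**The test is valid.** A reader might infer that chance baseline imbalance in a genus would pass for a diet effect. Under random allocation the test's error rate already allows for such imbalance, and step 6 shows no inflation. This objection stands in full: the cost is power only.

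**The size is unknown.** No correlation is documented, and at r = 0 nothing is gained. The 1 − r² rule belongs to linear ANCOVA. The rank-ANCOVA simulation tracks it closely, but with continuous data and no excess of zero counts.

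**Country is not a microbiota-only gap.** The ANCOVA for the other outcomes has no country term either, so the contrast within Section 2.9.1 holds for baseline, age and sex only.

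**An article condenses.** A fuller plan may add detail. But this article already fixes the test, the multiplicity rule and the software, so it states a choice and does not merely leave one open.

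**Conclusion.** The point holds as one of efficiency. The only stated between-diet test of taxa uses neither the V1 sample nor country in any stated way, although both will be available without extra collection. Under the assumptions shown, adjusting for V1 is worth 0% to 96% in effective sample size for r between 0 and 0.7, or 0 to 18 points of power for a 0.4 SD effect with 96 per arm. Country adds something if it explains part of the variance. The documents do not support a claim of bias, of false diet effects or of any harm to the primary BMI z-score analysis. This is a nearly free improvement to a secondary outcome that carries a stated mechanistic aim.

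**What to change.** Amend the metagenomics sentence in Section 2.9.1 before the data are analysed. For each taxon, compare V3 abundance between diets, ranked or suitably transformed, in a model with diet as the factor and the V1 value, country, age and sex as covariates. Rank ANCOVA is one example. Keep Benjamini–Hochberg at a 5% false discovery rate across taxa, and name the visits used.

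Do not replace the present test by a Mann–Whitney test on V3 minus V1 change, which loses power when r is below about 0.5. Which transformation suits compositional data is a separate question that this point does not settle.

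The cost is a change of wording and a short script outside STAMP. No extra samples, visits or sequencing are needed. If r turns out near zero, almost nothing is lost.
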